### Concealment mechanism {16b}

Allocation concealment will be ensured using opaque, identical envelopes for all groups. Patients preoperatively enrolled in the study will be randomized prior to surgery but allocation is done in the operating theater at the time the decision to proceed with resection is made. This is done to reduce dropouts due to non-resections and to allow for an “opt out” in case of unexpected intraoperative findings.

### Implementation {16c}

The randomization will be performed by a research nurse who will not participate in patient care, patient allocation is done in the operating room by the leading surgeon.

## Assignment of interventions: blinding

### Who will be blinded {17a}

The DRAIN1 trial is an open-label trial.

### Procedure for unblinding if needed {17b}

As blinding is not applied, no unblinding procedures are included.

## Data collection and management

### Plans for assessment and collection of outcomes {18a}

Data is collected locally for the baseline variables as well as the outcomes as stated above. The data collection is done by surgeons and research nurses. The outcomes will be assessed as described below.

### Plans to promote participant retention and complete follow-up {18b}

Due to the short follow-up period (90 days), complete follow-up is anticipated without the need for specific retention measures. Since the intervention occurs as a single event during surgery, the dropout rate is expected to be low. Additionally, as the informed consent does not request permission to use previously collected data or gather additional data upon withdrawal, no specific plan exists for handling such data.

### Data management {19}

The data collected is entered in an electronic database that includes range checks as indicated; double entry will not be used.

### Confidentiality {27}

Every patient enrolled in the study is given a pseudonym and the code list for them is kept locked and only accessible to the involved researchers. The presentation of the results will be done for groups; thus, individual identities will not be revealed.

### Plans for collection, laboratory evaluation and storage of biological specimens for genetic or molecular analysis in this trial/future use {33}

No biological specimens or material is collected in the DRAIN1 trial.

## Statistical methods

### Statistical methods for primary and secondary outcomes {20a}

The statistical analysis will follow the intention-to-treat principle. Baseline characteristics will be presented as means with standard deviations or medians with interquartile ranges, depending on data distribution. The chi-square test will be used for categorical variables when the expected count is ≥ 5; otherwise, Fisher’s exact test will be applied. Logistic regression models will be used to estimate odds ratios for morbidity risk and drain use. Univariable and multivariable models will be employed to assess the impact of drain placement on outcomes.

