## Abstract

**Background:**

Routine use of surgical drains after abdominal operations has largely been abandoned over the past decades. Studies have failed to demonstrate benefits of routine drainage following liver, gallbladder, gastric, and colorectal surgeries.

Until recently, intraoperative placement of abdominal drains was the gold standard in pancreatoduodenectomies (PDs) due to concerns about uncontrolled postoperative pancreatic fistula (POPF). A large randomized trial in 2014 reported increased mortality in patients without postoperative drain placement. However, as the study did not stratify participants based on their preoperative risk of developing a POPF, further research is needed.

Limited evidence from a non-randomized cohort suggests that omitting drains may be safe in very low-risk settings. However, a larger comparative study, including a broader range of PD cases, is necessary to confirm these findings.

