### Sample size {14}

The sample size calculation is based on the primary endpoint: the complication rate classified according to the Clavien–Dindo classification. The study is powered to detect a reduction in overall morbidity from 50 to 35%, with 80% power and a 5% two-tailed significance level [32]. The estimate is based on previous publications [6, 8]. To achieve this, a total of 133 patients per group is required. To account for an anticipated 10% dropout and loss to follow-up rate, a total of 300 patients will be included in the study.

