## Assignment of interventions: allocation

### Sequence generation {16a}

Randomization will be conducted at each participating center by a research nurse using a computer-generated sequence with blocks of eight. Block randomization ensures balance between treatment groups and will be implemented at each site, with blocks of eight distributed accordingly. The research nurse responsible for randomization will not be involved in patient care to maintain allocation integrity. Since participating centers routinely perform either pancreatojejunostomy or pancreatogastrostomy as their standard reconstruction method, stratification for this factor is not required.

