### Methods for additional analyses (e.g., subgroup analyses) {20b}

The planned subgroup analysis to be performed is a separate analysis of the primary end-point in patients having pancreatojejunostomy and pancreatogastrostomy, respectively. 

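### No primary model or covariates are named although allocation is blocked by site and the risk score is known for all, and separate PJ and PG analyses cannot show whether the effect differs

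*Protocol article*

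**What the plan says.** Protocol article, Statistical methods {20a}: the analysis follows intention to treat. "The chi-square test will be used for categorical variables when the expected count is" at least 5, and Fisher's exact test is used otherwise. The same paragraph adds logistic regression for odds ratios of morbidity, with univariable and multivariable models for the effect of drain placement. It lists no covariates and does not say which result carries the conclusion. The abstract's Methods paragraph says the groups are compared by chi-square and Fisher's exact test, and gives regression the task of producing odds ratios.

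Sequence generation {16a}: "Block randomization ensures balance between treatment groups and will be implemented at each site, with blocks of eight distributed accordingly". It also says that each centre routinely uses one of the two reconstructions, so no stratification for reconstruction was thought necessary.

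Inclusion criteria {10}: a risk score of 10 or less, built from body mass index and duct width, is required, so the score is known for every patient before surgery.

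Additional analyses {20b}: the planned subgroup analysis is "a separate analysis of the primary end-point in patients having pancreatojejunostomy and pancreatogastrostomy, respectively". No interaction test is mentioned.

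Sample size {14}: "The study is powered to detect a reduction in overall morbidity from 50 to 35" per cent, "with 80% power and a 5% two-tailed significance level"; "a total of 133 patients per group is required".

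**The concern.** There are two linked issues.

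First, the only hypothesis tests named use neither the randomisation stratum (site) nor the baseline score that defines the trial population. Multivariable models are also planned, but without covariates and without a rank. Chi-square, univariable and multivariable results could therefore all be reported for the same endpoint in an open-label trial. Naming one adjusted model removes that choice and may gain some precision.

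Second, two subgroup results read side by side do not answer whether the effect of omitting a drain depends on the reconstruction. Each half is underpowered, so one significant and one non-significant result is a common outcome even when the true effect is the same. That pattern could be published as a finding that drains matter for one type of anastomosis only. Because reconstruction follows centre, even a real difference between subgroups could be a difference between centres.

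**Working it through.** **Inputs from the Sample size section.** Control risk p1 = 0.50, no-drain risk p2 = 0.35, two-sided 5%, 133 per group (266 in all), 10% dropout, 300 recruited.

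**The plan's own figure.** With pooled variance,

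n = [z_a·√(2·p̄·q̄) + z_b·√(p1q1 + p2q2)]² / (p1 − p2)²

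where p̄ = 0.425, √(2 × 0.425 × 0.575) = 0.6991 and √(0.25 + 0.2275) = 0.6910.

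- Two-sided 5%: (1.960 × 0.6991 + 0.8416 × 0.6910)² / 0.0225 = 169.3, so 170 per group.
- One-sided 5%: (1.645 × 0.6991 + 0.8416 × 0.6910)² / 0.0225 = 133.3, so 134 per group.
- Dropout: 266 / 0.9 = 295.6, so 296; the plan rounds up to 300.

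The stated 133 is therefore not reproduced at the stated two-sided level. That is a separate matter. It enters here only because it sets the starting power.

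**Unadjusted power at 133 per group.** Power = Φ{[0.15·√n − 1.960 × 0.6991] / 0.6910}. With n = 133 this is Φ{(1.730 − 1.370) / 0.6910} = Φ(0.520) = 69.9%.

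**What adjustment could add.** The protocol article gives no number of sites, between-site variance or prognostic strength for the score, so all three are assumptions: four about equal sites, site SD on the logit scale of 0 to 0.6, and an odds ratio per SD of score of 1.0 to 2.2. Each setting used 3,000 simulated trials of 266 patients, allocated in blocks of eight within site, with marginal risks held at 50% and 35%. Monte Carlo error is √(0.7 × 0.3 / 3000), about 0.8 points. Entries are power in %, unadjusted chi-square / logistic model on arm, score and site:

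| Site SD | OR 1.0 | OR 1.35 | OR 1.65 | OR 2.23 |
|---|---|---|---|---|
| 0 | 70.4 / 70.3 | 71.7 / 72.1 | 71.2 / 72.7 | 70.5 / 75.5 |
| 0.3 | 71.5 / 71.8 | 71.2 / 71.7 | 71.8 / 74.8 | 71.4 / 76.9 |
| 0.6 | 71.3 / 73.5 | 70.8 / 73.8 | 72.7 / 75.4 | 71.6 / 77.3 |

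The gain runs from nil to 77.3 − 71.6 = 5.7 points, and no setting reaches 80%. With no treatment effect, rejection rates were 4.1–5.5% unadjusted and 4.6–5.6% adjusted, so both tests hold their level. A stronger assumption (five sites, log odds ratio 0.9 per SD, 2,000 trials) gave 70.0% against 78.8%, still short of 80%.

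**Separate PJ and PG analyses.** Assume the same true 50% versus 35% effect in both, and a two-sided 5% test in each. The PJ/PG split is not given, so a range is shown. For an equal split n = 66.5 per arm, and power = Φ{(0.15 × 8.155 − 1.370) / 0.6910} = Φ(−0.213) = 41.6%. P(exactly one significant) = a(1 − b) + b(1 − a).

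| Split | Power, larger (a) | Power, smaller (b) | Exactly one significant |
|---|---|---|---|
| 50:50 | 41.6% | 41.6% | 2 × 0.416 × 0.584 = 48.6% |
| 70:30 | 54.4% | 27.0% | 52.0% |
| 80:20 | 60.1% | 19.4% | 56.2% |
| 90:10 | 65.2% | 11.7% | 61.7% |

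With no effect in either subgroup, the chance of at least one significant result is 1 − 0.95² = 9.75%.

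**What an interaction can show.** At an equal split each subgroup risk difference has standard error √(0.4775 / 66.5) = 0.0847. Their difference has √2 × 0.0847 = 0.120, so the two effects must differ by about 1.96 × 0.120 = 0.235, or 23 to 24 points, to be significant. An interaction test is imprecise too. But when the effects are identical it signals a difference in about 5% of trials by design, whereas the side-by-side reading gives discordant results in 49% or more.

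**The case against.** The strongest reply is that adjusted analysis is already planned: the paragraph with the chi-square rule also commits to multivariable logistic models. A reader might infer that the primary comparison is solely an unadjusted chi-square. The document does not support that, because the chi-square sentence is a general rule for categorical variables and no analysis is labelled primary. This part of the reply stands. An analysis plan that is not shown may also name the covariates. What remains is that the article's abstract gives the group comparison to chi-square and Fisher's exact test, and nothing ties site or score to it.

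A reader might also infer that the score is strongly prognostic. The article does not show this. The score predicts fistula, the endpoint is overall morbidity, and enrolment cuts the score at 10. Nor does the criticism of an earlier trial, "as the study did not stratify participants based on their preoperative risk of developing a POPF", oblige this trial to adjust: its stated response is to exclude high-risk patients.

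Using odds ratios with a sample size based on proportions is a reporting preference, not a contradiction.

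On subgroups, the article speaks of separate analysis, so separate significance tests are an inference. Blocking within site also means the arm comparison inside each subgroup is not confounded by centre; only the contrast between subgroups is. Both points stand. Neither makes separate analyses informative about whether the effect differs.

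**Conclusion.** The point holds as an avoidable weakness, not as an error that invalidates the trial. The unadjusted test keeps its 5% level. The gain from adjusting for site and score is 0 to about 6 points over the assumed range, and it depends wholly on prognostic effects that the document does not quantify. It would be wrong to conclude that adjustment repairs the power: at 133 per group it does not reach 80% in any setting tried.

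The subgroup part is firmer, because the article itself fixes the method. Under an identical true effect, discordant significance occurs in 49% of trials at an equal split and up to 62% at 90:10. These figures assume 266 analysed patients, the design risks in both subgroups, and a 5% test in each.

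**What to change.** - Prespecify one primary analysis: logistic regression by randomised arm, adjusted for site and the continuous preoperative risk score. Pool very small sites, preferably with sites using the same reconstruction. Keep the chi-square or Fisher test as supportive.
- Replace the separate PJ and PG comparison with a single arm-by-reconstruction interaction in that model. Show the subgroup estimates with confidence intervals descriptively, without separate significance claims.
- State that reconstruction follows centre, so an interaction cannot be separated from centre differences, and that the test will be imprecise.
- Optionally, report a standardised risk difference beside the odds ratio.

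The cost is wording in the analysis plan before database lock. Site and score are known at baseline; the only condition is that the score or its two components are stored, not just the eligibility decision. Recruitment stood at 220 of 300 in March 2025, with completion expected by the end of 2026.

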### Interim analyses {21b}

A safety data monitoring board will oversee patient outcomes and conduct an interim analysis. The study will be halted if severe morbidity (Clavien–Dindo > 3a) or mortality exceeds 50% of expected rates. The board will consist of two independent experts from different centers who are not involved in the study. They will communicate directly with the primary investigator about the timing and conduction of the interim analysis.

### Methods for additional analyses (e.g., subgroup analyses) {20b}

The planned subgroup analysis to be performed is a separate analysis of the primary end-point in patients having pancreatojejunostomy and pancreatogastrostomy, respectively. 

### Methods in analysis to handle protocol non-adherence and any statistical methods to handle missing data {20c}

Patients allocated to no-drain treatment but receiving a drain will be separately analyzed in addition to those being included in the intention-to-treat analysis of that group and the group also being analyzed in a per-protocol analysis. Missing data will not be imputed.

### Plans to give access to the full protocol, participant-level data, and statistical code {31c}

The full dataset will not be made public but may be available upon contact with the principal investigator.

## Oversight and monitoring

### Composition of the coordinating center and trial steering committee {5d}

The coordinating center is responsible for both local data collection and compiling data from all participating centers. The trial steering committee is also the project management group and includes a local principal investigator (PI) from each participating center to ensure continuous support and facilitate information exchange between sites. The committee meets twice per year, with additional meetings scheduled as needed. If the safety data monitoring board raises concerns, these will be addressed in an additional meeting of the trial steering committee.

### Composition of the data monitoring committee, its role, and reporting structure {21a}

The data monitoring committee consists of two experienced pancreatic surgeons from independent, non-participating centers. Severe complications are reported to the board within 72 h of identification, along with the updated number of enrolled patients. The board evaluates these cases as outlined in the “Interim Analyses” section and provides a recommendation to the principal investigator (PI) regarding whether the study should be continued or halted if necessary.

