### Frequency and plans for auditing trial conduct {23}

No audit, other than the continuous reporting of severe complications as described above, is planned in the DRAIN1 trial.

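### The safety threshold is a bare observed rate, and the sections disagree on how often it applies and whether it binds; checked at each report, it would often be crossed by chance

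*Protocol article*

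**What the plan says.** Four places in the protocol article bear on this point.

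- **Interim analyses {21b}** gives the criterion: "The study will be halted if severe morbidity (Clavien–Dindo > 3a) or mortality exceeds 50% of expected rates". Either limb, severe morbidity or mortality, is enough. The same section describes the activity in the singular: "A safety data monitoring board will oversee patient outcomes and conduct an interim analysis". It leaves the timing to communication between the board and the primary investigator.
- **Composition of the data monitoring committee {21a}** says when data arrive: "Severe complications are reported to the board within 72 h of identification, along with the updated number of enrolled patients". It says what is done with them: "The board evaluates these cases as outlined in the “Interim Analyses” section". The output is a recommendation to the principal investigator "regarding whether the study should be continued or halted if necessary".
- **Composition of the coordinating center and trial steering committee {5d}** sends any concern of the board to an additional steering committee meeting.
- **Frequency and plans for auditing trial conduct {23}** plans no audit beyond "the continuous reporting of severe complications".

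**The concern.** The only evaluation criterion in the interim-analysis section is the rate threshold. If the board evaluates reported cases as that section outlines, and receives an updated denominator with each report, the natural result is a running check of two crude proportions against constant cut-offs. Such a check starts at the first patients, where one event can exceed the cut-off, and it repeats at every event.

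A threshold that is often crossed without any excess risk is hard to use. Either a trial with the expected risk is stopped by chance, or the board overrides its only written criterion case by case and the criterion no longer separates signal from noise. This matters here because the background section cites an earlier multicenter trial with higher mortality in patients without drains.

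The problem is distinct from the wording of the threshold. Read literally, the text halts the trial above half the expected rate. Changing that to 50% above expected would leave the repeated looks and small denominators as they are.

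**Working it through.** **1. The sections side by side**

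| Question | Reading A | Reading B |
|---|---|---|
| How often is the threshold applied? | At each report (data monitoring section: 72 h, running denominator, evaluation as in the interim section) | Once, at a time to be agreed (interim section, singular wording) |
| Does it bind? | Yes (interim section: the study will be halted) | No (data monitoring section: a recommendation; steering committee section: a further meeting) |

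The text does not choose between A and B on either row.

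**2. Inputs**

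- Maximum 300 patients (sample size section).
- Two limbs joined by *or* (interim section).
- Cut-off taken as 1.5 × expected, the more lenient reading of the wording.
- Expected rates are not given. Assumed: severe morbidity pS = 10–30%, mortality pD = 2–5%, with deaths counted among severe events.
- True risk set equal to expected risk, so every crossing is false.
- Lag L, the number of patients by which the enrolled count runs ahead of the reported case. Enrolment precedes surgery (concealment section) and follow-up lasts 90 days. Recruitment was 220 patients from May 2016 to March 2025: 220 / 106 months ≈ 2.1 per month. Three months is then about 3 × 2.1 ≈ 6 patients, so L from 0 to 6 was examined.

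The article states no false-halt probability, so there is no figure of its own to reproduce.

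**3. Why early looks dominate**

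With pD = 3% the mortality cut-off is 1.5 × 3% = 4.5%. One death among 22 patients is 1/22 = 4.55%, above the cut-off; 1/23 = 4.35% is below it. With no lag, any death among the first 22 patients crosses. At a true 3% risk the chance of that is 1 − 0.97^22 = 1 − 0.512 ≈ 49%, from one limb and the first 22 patients alone.

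**4. Whole trial, checked at each event**

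A crossing occurs at patient n, when that patient has an event, if

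S(n)/(n + L) > 1.5·pS or D(n)/(n + L) > 1.5·pD,

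where S and D are cumulative severe events and deaths, and the denominator is capped at 300. Simulation with 20,000–40,000 trials per scenario gave:

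| How the rule is applied | False-crossing probability over the assumed rates |
|---|---|
| Severe-morbidity limb only, L = 0 | about 0.60–0.65 |
| Mortality limb only, L = 0 | about 0.64–0.66 |
| Either limb, L = 0 | about 0.78–0.85 |
| Either limb, L = 3 | 0.63–0.77 |
| Either limb, L = 6 | 0.54–0.68 |
| Either limb, L = 0, no check before 50 patients | 0.36–0.54 |
| Either limb, L = 0, no check before 100 patients | 0.22–0.39 |
| Either limb, one look at 150 patients | 0.07–0.20 |

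Following a single arm of 150 patients with no lag gives 0.78–0.85, so the pooled or by-arm basis hardly changes the result. On the literal reading (above half the expected rate), the severe-morbidity limb alone is crossed in at least 99% of trials.

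**5. What remains at the current stage**

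With no lag, 72–80% of simulated trials crossed within the first 30 patients. For a trial that had not crossed by patient 220, the chance of a first false crossing in the last 80 patients is about 1–3%.

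**The case against.** A reader might infer that this trial would be halted about four times in five with no excess risk. The documents do not support that as a flat statement.

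- **Number of looks.** The interim section describes one analysis with timing to be agreed, which would be pointless if the rule ran at every report. Reported cases may simply feed that analysis, and the word continuous in the audit section describes reporting, not testing. This stands as a possible reading, and under it the figure is 7–20%. It does not remove the point, because the data monitoring section ties evaluation to the reported cases and the two sections then conflict.
- **Binding force.** The board recommends and the steering committee discusses, so a crossing need not stop the trial. This also stands, and for that reason the figures above are probabilities of crossing, not of halting. It contradicts the mandatory wording of the interim section.
- **Denominator.** The number enrolled runs ahead of the cases reported, so the no-lag figure is an upper one. This stands. With 6 patients ahead, more than half of trials without excess risk would still cross.
- **Details left elsewhere.** Expected rates, a minimum number of patients and a false-halt rate may sit in a fuller protocol or a monitoring charter, and their absence from an article is no fault. The point rests instead on what the article does state: a bare threshold and when cases are evaluated against it.
- **A sensitive early trigger may be deliberate**, given the earlier mortality signal. That is a legitimate choice if its false-alarm rate is known.

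Nor does the fact that 220 patients are enrolled show that the rule was ignored. The documents do not say how it has been applied.

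**Conclusion.** The point holds in conditional form. The sections disagree on how often the threshold applies and whether it binds, and the threshold itself allows for no sampling error. Applied at each report at 1.5 × expected, it would be crossed in about 54–85% of trials with exactly the expected risk. The top of the range has no lag; the bottom has the enrolled count 6 patients ahead. One look at 150 patients gives about 7–20%. These figures rest on assumed expected rates, on counting both limbs and on the lenient reading of the wording. The no-lag result depends little on the assumed rates.

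Because most false crossings fall early and recruitment stood at 220 of 300 in March 2025, the remaining numerical effect is small. What is left concerns mainly how monitoring is conducted and reported from here.

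**What to change.** Reconcile the interim-analysis, data monitoring and steering committee sections:

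1. Keep the 72-hour reports for individual case review.
2. State that the formal criterion is evaluated only at prespecified numbers of patients, against written expected rates.
3. Use a boundary that allows for sampling error and for the number of looks, calibrated by simulation or a sequential method.
4. State its false-halt probability under the expected rates and its chance of halting under a stated excess.
5. State whether the criterion is binding or advisory.

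The tolerated excess and the follow-up required at each look are for the sponsor and the board to choose.

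The cost is a short amendment and a small simulation. The downside is that a single early event no longer formally triggers the criterion and the formal check comes later, more so if complete 90-day follow-up is required. Case review of every report continues meanwhile. The final report should say how the threshold was applied up to the change.
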